### Status

Inclusion began right before the Corona epidemic set in. The study was therefore paused and has now been re-initiated in January 2023. Presently, 40 patients are included (10% accrual) and the study will continue until full accrual (400 patients) have been reached in 2026, with a follow-up period of additional three years. The primary endpoint is expected to be reached and ready for publication in 2029.

### Sample collection

All patients will have blood samples collected at baseline, week 12, and week 24. Rectal swabs are taken as a proxy for stool samples at baseline and week 12. At baseline, a fresh frozen tumor core biopsy is seeked to be obtained and for Arm A biopsies from the nephrectomy specimen will be fixed and stored according to the Danish Cancer Biobank for future analyses. All samples will be anonymously labeled with a pseudo patient study identifier. See Fig. 1.

### Experimental plans

ctDNA will be detected and measured in plasma samples using sequence-based methods.Bacterial species will be identified using 16 s ribosomal RNA gene sequencing and linked to response data to determine the role of the colonic microflora in immunotherapy response.The beta chain gene repertoire of T cell receptors will be sequenced to determine T cell clone dynamics and composition.Whole exome and genome sequencing will be applied to explore and validate predictive markers of treatment response.RNA-sequencing will be performed to investigate the association between molecular subtypes, immune subtypes, and gene expression signatures of cellular processes and treatment response.

### Statistical analyses

#### Sample size determination

Sample size calculations are based on simulated survival data and cox regression. With the assumption that 60% of patients meet the randomization criteria, and to demonstrate a 50% improvement in OS, with a 3-year follow-up, a sample size of 400 patients is needed to achieve 80% power at a 5% significance level. Hence, 400 patients will be included in NORDIC-SUN with the estimation of 240 patients (60%) being randomized (120 in each arm) and 168 occurred deaths upon reach of appropriate power.

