### Randomization and masking

Patients are randomized 1:1 into the two treatment arms:ARM A: 3 months of IO-IO or TKI-IO followed by deferred CN, followed by maintenance nivolumab or a TKI-IO-combination.ARM B: No surgery, 3 months of IO-IO or TKI-IO followed by maintenance nivolumab or a TKI-IO-combination.

Patient eligible for surgery is randomized by a local project nurse using a computer-generated allocation sequence and is not blinded due to the circumstances; surgery versus no surgery. In Arm A patients are treated according to standard protocol with first-line IO-IO or TKI-IO combination treatment followed by a CN. In Arm B patients are receiving standard IO-IO or a TKI-IO combination first-line treatment (Fig. 1). Patients will be stratified by treatment choice (IO-IO vs TKI-IO).

The remaining patients, referred to as Arm C, not eligible for randomization due to > 3 IMDC risk factors, progressive disease at metastatic sites, poor performance or a non resectable tumor will undergo three months of nivolumab or a TKI-IO combination and then be evaluated again after another 3 months. If still not eligible for randomization, the patients will continue nivolumab maintenance and TKI-IO combination and be followed on survival.

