#### Data analysis

Difference in primary and secondary endpoints between the two treatment arms will be tested with a two-sided log rank test at the 5% alpha level. Statistical methods including Kaplan–Meier and cox proportional hazard regression will be performed adjusted and unadjusted for the stratification factor. Furthermore, linear regression, logistic regression, and machine learning approaches (e.g. Random Forest, Neural Networks, and Gradient Boost models) will be applied in an exploratory manner to identify any correlation between molecular measures and clinical outcome parameters.

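### On the usual reading of a 50% improvement in OS (HR 0.667), 168 deaths give about 75% power, not 80%; the effect, death count and power should be made to agree

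*Protocol article*

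**What the plan says.** Under Sample size determination, the article reports a calculation by simulated survival data and Cox regression. It assumes that 60% of enrolled patients can be randomised and concludes that "to demonstrate a 50% improvement in OS, with a 3-year follow-up, a sample size of 400 patients is needed to achieve 80% power". The alpha used for this is 5%. The paragraph then expects "240 patients (60%) being randomized (120 in each arm) and 168 occurred deaths upon reach of appropriate power".

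Two other places fix the remaining inputs. Randomization and masking says: "Patients are randomized 1:1 into the two treatment arms". Data analysis says that differences between the arms "will be tested with a two-sided log rank test at the 5% alpha level".

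The article gives no hazard ratio, control-arm median or survival distribution for the simulation.

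**The concern.** For a 1:1 log-rank or Cox comparison under proportional hazards, power depends almost entirely on the number of deaths, the hazard ratio and alpha. The article states the deaths, the alpha and the power, and describes the effect in words. Taken in its ordinary sense, that description does not lead to the stated power at the stated number of deaths.

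This is the only power statement for the primary endpoint, and 168 is the death count that the article links to adequate power. On the ordinary reading, the chance of missing the target benefit at 168 deaths is about 25% rather than 20%.

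**Working it through.** **Inputs from the article.** 400 enrolled, of whom 60% randomised: 0.60 × 400 = 240, or 120 per arm. Deaths: 168, and 168/240 = 70%. Alpha 5%, two-sided log-rank test. Power 80%. Allocation 1:1.

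**Input assumed.** A 50% improvement in OS means a 1.5-fold survival time. With proportional hazards and exponential survival, HR = 1/1.5 = 0.667 and ln(1.5) = 0.4055.

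**1. What the stated pair implies.** With 168 deaths and 80% power, the detectable HR = exp(−2 × (1.960 + 0.842)/√168) = 0.649. Since 1/0.649 = 1.54, this is a 54% improvement under exponential survival. Checked directly, HR 0.65 needs 170 deaths and has 79.7% power at 168.

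**2. Deaths needed for HR 0.667.**
- Schoenfeld: 4 × (1.960 + 0.842)² / 0.4055² = 190.97, so 191.
- Freedman: ((1 + 0.667)/(1 − 0.667))² × (1.960 + 0.842)², rounded up, gives 197.
- As a share of those randomised: 191/240 = 80%, against the planned 70%.

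**3. Power at 168 deaths for HR 0.667.**
- Schoenfeld: Φ(√168/2 × 0.4055 − 1.960) = 74.8%.
- Freedman: Φ(√168 × 0.333/1.667 − 1.960) = 73.6%.

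**4. Whether sizing by simulation explains the gap.** These are log-rank simulations with exponential survival, 120 per arm, uniform accrual and analysis at a fixed number of deaths. Control medians and accrual periods are assumptions.

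| Control median | Accrual | Runs | Power at 168 deaths | Power at 191 deaths |
|---|---|---|---|---|
| 12, 15, 18, 24 months | 36 months | 4,000 each | 73.8 to 74.0% | 80.0% (median 18) |
| 24 months | 36 months | 8,000 | 73.8% | 79.4% |
| 27 months | 48 months | 20,000 | 74.6% | 79.7% |

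Simulation agrees with the formulas, and the assumed median makes almost no difference once the death count is fixed.

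**5. Two simple alternatives.**
- One-sided 5%, HR 0.667: 4 × (1.645 + 0.842)²/0.4055² = 150.4, so 151 deaths; power at 168 is 83.7%. This does not give 168, and Data analysis says two-sided.
- A 50% reduction in hazard (HR 0.5): 66 deaths; power at 168 is 99.4%.

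**6. Whether 240 patients can supply 191 deaths.** With HR 0.667, an assumed 36-month accrual and 36 months of further follow-up, the expected deaths are about 193 for a control median of 18 months and about 171 for 24 months. The answer depends on a median that the article does not state.

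**The case against.** The strongest objection is that HR 0.667 is an interpretation. The article gives no hazard ratio, and turning a 1.5-fold survival time into 0.667 requires exponential survival, which simulated data need not follow. Two ordinary meanings of the phrase can give 80% power at 168 deaths:

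- **A 50% longer median with a slightly rising hazard.** For Weibull survival, HR = 1.5^(−k). A shape k of 1.07 gives HR 0.648 and 80.3% power at 168 deaths. Shape 1.0 gives 74.8% and shape 1.1 about 82%.
- **A 50% relative rise in 3-year survival**, which the mention of 3-year follow-up in the same sentence could suggest. A rise from 31.5% to 47.25% gives HR = ln(0.4725)/ln(0.315) = 0.649 and 80.0% power at 168 deaths. A control rate of 28% gives 70%, 30% gives about 76% and 35% gives 89%.

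This much stands: a reader might infer that no reading reconciles 168 deaths with 80% power, and that inference is wrong. But both readings work only for a narrow choice of an input that the article does not report. They show that the figures could be consistent, not that they are.

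It is also fair to say that simulation inputs usually sit in the full protocol or analysis plan, and their absence from an article is not the point here. The point is that the three figures the article does publish do not fit together on the reading most readers will take.

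**Conclusion.** The inconsistency holds conditionally. With HR 0.667, proportional hazards, roughly exponential survival and a two-sided 5% test, power at 168 deaths is about 75%, a shortfall of about 5 percentage points, and 80% needs about 191 deaths (197 by Freedman). The 168 deaths match 80% power only for HR about 0.65.

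Three stronger conclusions are tempting, and the article does not support them:

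- **That the trial is too small.** The check concerns the death count. Whether 240 patients can yield 191 deaths by a given date depends on the unreported control median.
- **That 191 deaths must be adopted.** If the simulation used HR near 0.65, the death count and the power are right, and only the description of the effect is wrong.
- **That a null result would be misread as evidence against surgery.** Interpretation will rest on the estimate and its confidence interval, which planned power does not change.

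This is a correction worth making to the primary endpoint's only power statement. It does not invalidate the design.

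**What to change.** Look up the hazard ratio and survival distribution used in the simulation. State the target as that hazard ratio, then make effect, deaths and power agree:

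- **If the design HR is 0.667:** either restate power at 168 deaths as about 75%, or keep 80% and set the primary analysis at about 191 deaths in the same 240 patients. The first costs one sentence and a less favourable power figure. The second needs no more patients but means a later analysis, by an amount that depends on the control-arm death rate.
- **If the design HR is about 0.65:** keep 168 deaths and 80% power, and replace the 50% wording with that hazard ratio and the survival assumption behind it. This costs one sentence.

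The change is easy now: Status reports 40 patients included (10% of 400) and full accrual planned for 2026.

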#### Data analysis

Difference in primary and secondary endpoints between the two treatment arms will be tested with a two-sided log rank test at the 5% alpha level. Statistical methods including Kaplan–Meier and cox proportional hazard regression will be performed adjusted and unadjusted for the stratification factor. Furthermore, linear regression, logistic regression, and machine learning approaches (e.g. Random Forest, Neural Networks, and Gradient Boost models) will be applied in an exploratory manner to identify any correlation between molecular measures and clinical outcome parameters.

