### Detailed enrollment criteria are listed below

*Inclusion criteria:*
Synchronous mRCC proven with a core needle biopsy (all histological subtypes are acceptable) and measurable as per RECIST v 1.1.Age > 18.Patients referred to standard immunotherapy-based first-line treatment according to the recommendations by the European Medicines Agency and the national health authorities. Both IO-IO and TKI-IO are considered as a standard treatment.Females not pregnant. Fertile patients must use effective means of contraception.Life expectancy > 4 months.Karnofsky Performance status > 70.Laboratory values acceptable for IO-IO or TKI-IO treatment.Able to speak and understand native language.
*Exclusion criteria:  *
Prior systemic treatment for mRCC.Other cancer diagnosis within three years (except in situ basal cell carcinoma and radically treated localized prostate cancer with undetectable prostate-specific antigen).Major surgical procedure, open surgical biopsy, or significant traumatic injury within 14 days prior to enrollment, or non-healed lesion.Clinically significant (i.e. active) cardiovascular disease for example cerebrovascular accidents (< 6 months before inclusion), myocardial infarction (< 6 months before inclusion), unstable angina, New York Heart Association grade II or greater congestive heart failure.No symptomatic brain metastasis requiring systemic corticosteroids (> 10 mg daily prednisone equivalent).Recent (within the 30 days prior to inclusion) treatment with another investigational drug.Any active or recent history of a known or suspected autoimmune disease or recent history of a condition that requires systemic corticosteroids (> 10 mg daily prednisone equivalent) or other immunosuppressive medications, excluding inhaled steroids and local cutaneous steroids. Subjects with vitiligo or type I diabetes mellitus or residual hypothyroidism due to autoimmune thyroiditis only requiring hormone replacement, psoriasis not requiring systemic treatment are permitted to enroll.Known hypersensitivity to monoclonal antibodies.Known history of testing positive for human immunodeficiency virus or known acquired immunodeficiency syndrome (AIDS).Any positive test for hepatitis B- or C-Virus, indicating acute or chronic infection.

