### Study procedure

Patients included in the NORDIC-SUN trial are stratified according to institution, treatment choice, number of IMDC risk factors, and combined elevated neutrophil–lymphocyte ratio and hyponatremia.

All patients will receive systemic IO-IO or TKI-IO immediately after inclusion. After three months of nivolumab combined with ipilimumab or a TKI-IO combination, the patient will be discussed for resectability at the multidisciplinary meeting (MDT), whether the patient is eligible for CN. Patients with ≤ 3 IMDC risk factors and deemed suitable for CN including an acceptable performance status and absence of progression at metastatic sites will then undergo randomization. Patients deemed not suitable for surgery or have > 3 IMDC risk features at the 3 month evaluation continue systemic therapy for 3 months, followed by a 2nd evaluation 6 months after inclusion. Patients with ≤ 3 IMDC risk factors and deemed suitable for CN at 2nd evaluation will then undergo randomization. Patients deemed not suitable for surgery or have > 3 IMDC risk features at the 6 month evaluation continue systemic therapy (Arm C). Nivolumab may continue until unacceptable toxicity or total treatment length of two years from inclusion. Allocating patients to Arm C promotes participant retention, securing outcome data of patients not randomized.

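### The OS analysis adjusts at most for the stratification factor and leaves out response before randomization and histology: valid, but less efficient than it could be

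*Protocol article*

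**What the plan says.** In the protocol article, Data analysis says that differences between the arms "will be tested with a two-sided log rank test at the 5% alpha level". It then lists further methods, among them that "cox proportional hazard regression will be performed adjusted and unadjusted for the stratification factor". It names no other covariate for the arm comparison, and it does not say whether the adjusted or the unadjusted Cox result leads.

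The stratification is described twice. Study procedure lists institution, treatment choice, number of IMDC risk factors, and a combined neutrophil–lymphocyte ratio and hyponatremia factor. Randomization and masking names treatment choice only. Neither contains response or histology.

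Randomization follows 3 or 6 months of systemic therapy. At the 3-month evaluation, patients with at most three IMDC risk factors who are suitable for surgery, including "an acceptable performance status and absence of progression at metastatic sites will then undergo randomization". On histology, the inclusion criteria require a core needle biopsy and add that "all histological subtypes are acceptable".

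**The concern.** The randomized set mixes patients with an objective response and patients who have merely not progressed at metastatic sites. It also mixes all histologies. The article itself treats both as relevant: its Background says that current recommendations for nephrectomy depend on a response to systemic therapy, and its secondary endpoints include survival by clear cell and non-clear cell histology.

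In a Cox model, leaving out a strong prognostic covariate pulls the estimated treatment hazard ratio towards 1 and lowers power, even when the arms are balanced. The log-rank test, which uses no covariates, shares this loss. The comparison rests on a planned 240 randomized patients and 168 deaths, so efficiency available without another patient is worth having. Because the trial is open label, covariates chosen after results are seen would carry little weight. They need to be fixed beforehand.

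**Working it through.** **Inputs from the article.** Two-sided 5% test. Aim: "to demonstrate a 50% improvement in OS, with a 3-year follow-up". Size: "the estimation of 240 patients (60%) being randomized (120 in each arm"). Events: "168 occurred deaths upon reach of appropriate power". Power claim: "a sample size of 400 patients is needed to achieve 80% power at a 5% significance level".

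**The article's own figure.** 400 × 0.60 = 240, and 168/240 = 70%, as stated. The article gives no hazard ratio; a 50% improvement is read here as HR = 1/1.5 = 0.667, with ln 1.5 = 0.4055.

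- Deaths for 80% power (Schoenfeld): 4 × (1.960 + 0.842)² / 0.4055² = 191. Freedman's formula gives 197.
- Power with 168 deaths: √168/2 × 0.4055 − 1.960 = 2.628 − 1.960 = 0.668, which is 74.8%.

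The stated 80% is therefore not reproduced at HR 0.667 (HR 0.65 would give 79.7%). That is a separate matter. Here it supplies the benchmark of about 75%.

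**Are both values available before allocation?** Histology comes from the entry biopsy. For response, the qualifying evaluation must judge progression at metastatic sites, disease must be measurable by RECIST 1.1 at entry, and RECIST response rates are secondary endpoints. The article does not say that a full RECIST category is recorded at the qualifying visit, but these data should allow it.

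**Simulation.** 240 patients, 1:1, exponential survival, analysis at the 168th death, conditional treatment HR 0.667, 3,000 trials per row (Monte Carlo error about 1 point). Assumed, not from the article: 45% responders; one binary stratification factor (IMDC) with HR 1.5 and 40% prevalence; and the prognostic effects in the first two columns.

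| Response HR | Non-clear-cell HR (share) | Log-rank | Cox, stratification factor | Cox, plus response and histology | Gain over stratified Cox | Gain over log-rank |
|---|---|---|---|---|---|---|
| 0.7 | 1.2 (10%) | 71.3% | 72.4% | 74.3% | 2 | 3 |
| 0.6 | 1.3 (15%) | 70.5% | 72.4% | 75.2% | 3 | 5 |
| 0.5 | 1.5 (15%) | 68.7% | 69.2% | 75.4% | 6 | 7 |
| 0.4 | 1.5 (15%) | 63.3% | 64.1% | 73.6% | 9.5 | 10 |
| 0.3 | 2.0 (20%) | 57.0% | 57.2% | 73.0% | 16 | 16 |

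The mechanism shows in the average fitted hazard ratios. From the first row to the last, the stratification-adjusted model drifts from 0.670 to 0.717, while the fuller model stays between 0.661 and 0.666.

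**Sensitivity.**

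- With conditional HR 0.65, the gains over the stratified Cox run from about 0 to 16 points.
- With the stratification-adjusted HR held near 0.667, the last four rows gain 3, 5, 9 and 15 points.
- A simulation with three stratification covariates (IMDC number, neutrophil–lymphocyte ratio with hyponatremia, treatment choice), about half responders and 15% non-clear cell at HR 1.5 moved power from 68.9% to 71.1%, 68.3% to 74.8% and 64.5% to 73.9% for response HRs of 0.65, 0.50 and 0.40.

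**Type I error.** Under the null, the log-rank test, stratified Cox and fuller Cox rejected in 5.6%, 5.4% and 5.9% of trials. In a simpler simulation with response and histology as the only covariates, the unadjusted and adjusted rates were 4.8% and 5.2%. The adjusted rate is thus up to half a point above its comparator. Half a point is worth about 1.3 points of power near the benchmark: the critical value falls from 1.960 to 1.919, and 2.628 − 1.919 = 0.709 gives 76.1% against 74.8%. The gain in the weakest row is therefore close to noise; the gains for response HRs of 0.5 and below are not.

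**The case against.** The strongest objection is that the article tests with a log-rank test. Adding covariates to a Cox model reported beside it leaves that test's power unchanged. This stands, and it decides what the fix must contain. A reader might infer that one more sentence about Cox covariates recovers the power; the documents do not support that.

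Second, a log-rank test with a stratification-adjusted Cox model is conventional and valid. This also stands. A reader might take the omission for an error, or think that nothing controls response depth between the arms. Randomization balances it in expectation, and the 5% error rate already allows for chance imbalance.

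Third, the size depends on the inputs chosen. The article gives no responder share, no non-clear-cell share and no hazard ratio for either factor. A reader might quote a fixed loss of several points as a property of this trial; only an assumed range can be given.

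Fourth, a covariate of response versus stable disease does not fit everyone who may be randomized. Eligibility excludes progression at metastatic sites only, so a patient whose primary tumor alone has progressed could enter and would have no category. The 6-month wording in Study procedure also does not repeat the condition on progression. This stands and is met by how the levels are defined.

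Fifth, covariate lists often belong in an analysis plan, and the full protocol and SAP are not shown. They may go further. But the article does state an adjustment set, and the point concerns that stated choice rather than a missing detail.

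**Conclusion.** The point holds as a recommended gain in efficiency, not as a correction of an error. The stated adjustment stops at the stratification factor, neither description of the stratification contains response or histology, and both can be fixed before allocation. With 168 deaths and a conditional HR of 0.667, adding both to a stratification-adjusted Cox model is worth about 2 to 10 points of power for assumed response HRs of 0.7 to 0.4, and about 0 to 16 points over wider assumptions. The direction is consistent across the simulations; the size rests on assumed prognostic strengths and prevalences. The power is gained only if the adjusted test is the primary test.

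Two nearby matters are separate and lend this point no support: the 168 deaths fall short of 80% power at HR 0.667, and the two descriptions of the stratification differ.

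**What to change.** Before outcomes are known, prespecify for overall survival a Cox model with treatment, the stratification factors and two further covariates:

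1. histology, clear cell versus non-clear cell;
2. response at the qualifying 3- or 6-month evaluation, complete or partial response versus no response, with any randomized patient showing primary-tumor progression placed in the no-response level.

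Name the treatment test from this model as the primary test and keep the log-rank test as supportive. If the team prefers to keep the log-rank test as primary, the same model can still be reported, but it should be described as improving the treatment estimate and its robustness to chance imbalance, not the power of the test. In either case, state which stratification factors the model contains.

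The cost is a few sentences, plus making sure that the response category is recorded before allocation. No extra patients, biopsies or scans are needed. The Status section reports 40 of 400 patients included, so at that stage the change could be made in time. The drawback is interpretive: the hazard ratio becomes conditional on these factors, and the report must say so.
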